**Secondary outcomes:**

- The recanalization rate of targeted vessels after thrombectomy.
- The recanalization rate of targeted vessels at the end of endovascular treatment.
- The recanalization rate of targeted vessels at 24-72 hours.
- Symptomatic intracranial hemorrhage within 72 hours.
- 90-day functional outcomes (dichotomized 90-day mRS, ordinal scale of 90-day mRS).
- Death at 90 days.
- Number of thrombectomy passes required.

**10. Data collection and follow-up**

The study sites are required to collect data on patients at baseline (before randomization); treatment period (day 0; the day of randomization); 24-72 hours after randomization; day 7 (or at discharge if discharged earlier) and 90 days ( $\pm 7$  days) after randomization. All SAEs including death within the 3-month follow-up period are recorded. The assessments at 90-days are to be undertaken by a well-trained investigator, who is blind to treatment allocation, either face to face or by telephone. Source documents, such as patient interview records or questionnaire responses, can be directly entered into the database. Paper case report forms can also be filled in and retained as source documents. Brain imaging will be collected at baseline, during the treatment period, and 24-72 hours ( $\pm 8$  hours). If clinically indicated, patients may receive further brain imaging scans at a later stage. Brain imaging data are collected by each site. The leading site assists each site in uploading image data. After uploading, the leading site is responsible for image analysis.

90-day follow-up is required for all participants in this study. If they die before 90 days, they will be followed up until death. Patients who do not comply with the protocol

and/or terminate the assigned treatment regimen also need to be followed up for 90 days, as their data will be required for the intention-to-treat analysis. The study flow chart lists the types of data and the schedule of evaluation. The leading site will provide the paper version of the case report form and the instruction manual for reference, as well as the guidelines of the case report form and the definition of terms.

### ***10.1 Patient Contact Details log***

Each center will keep a record of the contact details and information of next-of-kin for all patients recruited into the study. This will be kept with the patient file in the participating center in a locked filing cabinet in accordance with local privacy and confidentiality policies. The patient contact detail log will also be used to record any issues in the process of informed consent, work done during follow-up, and protocol violations. This will be used by the local research coordinator and PI to record the management of the informed consent process, and follow-up arrangements, and respond to queries from the leading center.

### ***10.2 Randomization assessment***

All patients with acute ischemic stroke due to large artery occlusion will be assessed for eligibility for the study using a checklist of the criteria described previously. The enrollment and randomization log should be kept in a locked filing cabinet within each participating center.

The log should include:

- Patient demographic information: sex, date of birth, time of onset (or last seen without symptoms), time of admission, NIHSS before randomization, pre-stroke mRS.
- Imaging evaluation before randomization: CTP time, occluded vessel, penumbra volume, core infarct volume, and mismatch ratio.
- Randomization stratification information: site number.

- Inclusion and exclusion criteria checklist.
- Randomization information.

### ***10.3 Baseline data***

- Medical history: hypertension, diabetes mellitus, stroke, ischemic heart disease, hypercholesterolemia, smoking and drinking history, coagulation dysfunction or other blood diseases, history of gastrointestinal or urinary tract bleeding, previous oral drugs (aspirin, clopidogrel, warfarin, antihypertensive drugs, lipid-lowering drugs, antidiabetic drugs), etc.
- Vital signs: blood pressure, heart rate (HR), weight, height, GCS, and NIHSS at admission.
- Blood test results:
  - Full blood count: red blood cells, white blood cells, neutrophils (count, percentage), hematocrit, hemoglobin, platelets.
  - Serum biochemistry: renal function: creatinine, urea (or urea nitrogen), uric acid; liver function: glutamic oxaloacetic transaminase, glutamic pyruvic transaminase; glucose.
  - Coagulation function: PT, APTT, TT, FIB, INR, D-dimer, fibrin degradation products.
- Brain imaging: brain multimodal CT.

### ***10.4 Treatment information (0-24h)***

- Tirofiban administration information, including tirofiban intravenous bolus start time, intravenous bolus dose, intravenous infusion start time, and intravenous infusion end time. Ensure that the patient treatment complies with their randomization.
- Endovascular treatment information, including the mTICI grade of targeted vessels after the first angiography, mTICI grade of targeted vessels after the first-

pass thrombectomy, thrombectomy devices (second-generation, third-generation, aspiration or other), degree of stenosis after thrombectomy, number of thrombectomy passes, mTICI grade of targeted vessels after thrombectomy, use or otherwise of balloon dilatation or stent implantation, the final mTICI grade at the end of endovascular thrombectomy, and the final residual stenosis (0-30%; 30-50%; 50-70%, 70-99%). Intraoperative complications, femoral artery puncture time, DSA first angiography time, final recanalization time.

- Brain imaging: DSA collected the endovascular treatment process.
- Concomitant medication: antiplatelet drugs (aspirin, clopidogrel, cilostazol, others); Anticoagulant drugs.

## ***10.5 Follow-up data***

### **10.5.1 24-72 hours after randomization**

- GCS and NIHSS scores
- Brain imaging follow-up (brain non-contrast CT and CTA; if brain CTA cannot be acquired, brain MRA is acceptable; if the patient has extracranial occlusion of the internal carotid artery, it is necessary to acquire carotid artery CTA or MRA at the same time), and the AOL grade on the brain CTA or MRA
- Blood test results:
  - Full blood count: red blood cells, white blood cells, neutrophils (count, percentage), hematocrit, hemoglobin, platelet count;
  - Serum biochemistry: renal function: creatinine, urea (or urea nitrogen), uric acid; liver function: glutamic oxaloacetic transaminase, glutamic pyruvic transaminase; glucose.
  - Coagulation function test: PT, APTT, TT, FIB, INR, D-dimer, fibrinogen degradation products.

- Clinical safety events: gastrointestinal bleeding, urinary tract bleeding, thrombocytopenia, coagulation dysfunction.

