## ***7.2 Drug dosage and regimen***

**The study group:** intravenous tirofiban combined with thrombectomy. Tirofiban intravenous therapy is initiated within half an hour after randomization and before femoral artery puncture. Tirofiban is used as follows: tirofiban 10 µg/kg, intravenous bolus injection within 3 minutes, and 0.1 µg/kg/min intravenous infusion for 24 hours. The study group is required to maintain tirofiban medication for at least 24 hours according to the protocol. If intracranial hemorrhage is found in follow-up head CT or other serious adverse events (such as gastrointestinal or urinary tract hemorrhage) that may be related to tirofiban within 24 hours, the investigator may consider stopping the medication. The site investigators decide on the subsequent antiplatelet treatment plan based on the patient's condition after 24 hours of intravenous tirofiban infusion.

**The control group:** treated with routine thrombectomy. The control group is not allowed to use intravenous or intraarterial antiplatelet drugs before the first thrombectomy attempt. Other thrombectomy procedures are carried out in accordance with local guidelines. If there is obvious vascular stenosis or re-occlusion after thrombectomy, the operator can use other rescue measures according to the circumstances, including intra-arterial tirofiban treatment. The rescue treatment does not include an intravenous loading dose of tirofiban.

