## ***7.4 Procedural method***

It is recommended that the time from randomization to femoral artery puncture should be ≤ 90 minutes. During the procedure, all participants are required to undergo a first

thrombectomy attempt after cerebral angiography evaluation. After the first pass thrombectomy, the operator can determine the remaining procedural plan according to the procedural situation. The operator can use other rescue measures at his/her discretion, including balloon dilatation and/or stenting. The control group could use arterial tirofiban rescue treatment after the first pass of thrombectomy, while intra-arterial tirofiban treatment is not recommended for the study group.

Heparinization during the procedure is prohibited.

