## **3. Analysis**

The statistical analysis includes (1) the number of cases completed at each site and the withdrawal of cases; (2) analysis of demographics and baseline characteristics of patients in each group at the time of enrollment, and the comparability between the study group and the control group; (3) efficacy evaluation including the determination of efficacy endpoints and the efficacy comparison of each group; (4) safety evaluation including the comparison of laboratory results and clinical adverse reactions in each group.

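### The 24-72 h safety list names only gastrointestinal and urinary bleeding, so puncture-site and other extracranial bleeds that arise after the procedure and are not SAEs are not systematically captured

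*Protocol*

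**What the plan says.** **Events collected.** Protocol VI.10.5.1 gives one line for clinical events at the 24-72 h visit: "Clinical safety events: gastrointestinal bleeding, urinary tract bleeding, thrombocytopenia, coagulation dysfunction". Two kinds of bleeding are named, and there is no entry for other bleeding.

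**Exposure at puncture, study arm.** Protocol VI.7.2: "Tirofiban intravenous therapy is initiated within half an hour after randomization and before femoral artery puncture". On duration, the same section says: "The study group is required to maintain tirofiban medication for at least 24 hours according to the protocol".

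**Exposure at puncture, control arm.** Protocol VI.7.2: "The control group is not allowed to use intravenous or intraarterial antiplatelet drugs before the first thrombectomy attempt". After that, VI.7.4 permits some exposure: "The control group could use arterial tirofiban rescue treatment after the first pass of thrombectomy".

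**Other routes into the data.** VI.10 states: "All SAEs including death within the 3-month follow-up period are recorded". The procedure record in VI.10.4 includes: "Intraoperative complications, femoral artery puncture time, DSA first angiography time, final recanalization time".

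**Planned comparison.** XI.3 lists, as its fourth element, "safety evaluation including the comparison of laboratory results and clinical adverse reactions in each group".

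**The concern.** Tirofiban inhibits platelet aggregation, and every study-arm patient is due to have an arterial puncture while receiving it. Bleeding at or near the access site is an obvious event to ask about, yet the visit at which safety events are gathered does not name it. It has no field for bleeding at any site other than the gut and urinary tract.

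The trial is open-label (VI.1). If a groin haematoma is recorded only when someone judges it serious, ascertainment depends on a judgement made by staff who know the arm. The trial could then follow its plan exactly and report extracranial bleeding from an incomplete count. No later analysis plan can recover an event that was never recorded.

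**Working it through.** **1. The plan's own figure.** The only design figure is the sample size in XI.4, which sets the number available for any safety comparison. The inputs are 70% versus 50%, two-sided alpha 0.05, power 80% and 7% dropout. With pooled variance under the null and no continuity correction:

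n = [1.96 × √(2 × 0.60 × 0.40) + 0.8416 × √(0.70 × 0.30 + 0.50 × 0.50)]² / 0.20² = (1.358 + 0.571)² / 0.04 ≈ 93 per arm.

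93 / 0.93 = 100 per arm, 200 in total. The figure reproduces, and the present point does not touch it.

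**2. Is the list closed?** VI.10.5.1 has four items and no open-ended term. The protocol does use such terms elsewhere: the prohibited drugs in VI.7.5 and the medical history in VI.10.3 end with one, the concomitant drugs in VI.10.4 include a category for others, and XI.1 says its list of major violations is not exhaustive. The list is best read as complete.

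**3. How long does exposure last after puncture?** VI.7.2 starts the drug after randomization and before puncture. VI.7.4 recommends puncture within 90 minutes of randomization. If that recommendation is kept, at most 1.5 h of a 24 h infusion has run by puncture, so at least 24 − 1.5 = 22.5 h remain unless the drug is stopped early. The protocol gives no procedure duration, but the period at risk clearly extends beyond the procedure.

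**4. Which bleeds have a route in?**

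| Event | Route |
|---|---|
| Gastrointestinal or urinary bleed | Named in VI.10.5.1 |
| Bleed at any site meeting an SAE criterion | SAE form, VI.10 and VIII |
| Access-site bleed during the procedure | Can be entered as an intraoperative complication, VI.10.4 (not itemised) |
| Intracranial bleed | Blinded image reading, VI.6.2; symptomatic hemorrhage is an outcome, VI.9 |
| Puncture-site, retroperitoneal or other extracranial bleed after the procedure, below the SAE threshold | No named field |

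Hemoglobin is measured at baseline (VI.10.3) and at 24-72 h (VI.10.5.1). A fall can suggest blood loss but does not identify site or cause. The discharge form (VI.10.5.2) has no bleeding item. The flow chart (VII) has a row for SAEs and none for other adverse events.

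**5. What could a comparison show?** The documents give no rate for these bleeds. The rates below are assumptions, at 100 per arm and two-sided 0.05, using the same normal approximation.

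| Control | Tirofiban | Power |
|---|---|---|
| 2% | 5% | 21% |
| 2% | 8% | 49% |
| 2% | 10% | 67% |
| 5% | 10% | 27% |
| 5% | 15% | 66% |

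For 5% versus 10%: the null standard error is √(2 × 0.075 × 0.925 / 100) = 0.03725 and the alternative standard error is √((0.05 × 0.95 + 0.10 × 0.90) / 100) = 0.03708. Then z = (0.05 − 1.96 × 0.03725) / 0.03708 = −0.62, so power is about 27%. An observed 5-point difference would carry a 95% interval of 5 ± 1.96 × 3.708, about −2.3 to 12.3 points.

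**The case against.** The strongest reply is that the bleeds that matter most are already covered. A retroperitoneal bleed, or a haematoma that prolongs the stay, would ordinarily meet an SAE criterion in VIII.1, and SAEs are recorded for three months. Procedural complications are recorded in both arms, and laboratory results are compared by group. XIII asks sites to report adverse events in general terms, and VI.8.2 has withdrawing patients asked about them. VI.10 refers to a case report form and definitions of terms that are not shown and may hold such an item. The comparison would also be weak at this sample size.

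Much of this stands, and it limits the point. A reader might infer any of the following, none of which the documents support:

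- *Extracranial bleeding is not compared at all, or is recorded nowhere.* Step 4 shows several routes, and XI.3 does not limit its comparison to the four listed events.
- *The list is a list of non-serious events.* VI.10.5.1 attaches no severity, and VI.7.2 gives gastrointestinal and urinary hemorrhage as examples of serious events.
- *Control puncture sites are unexposed to tirofiban.* Some controls may receive it by artery after the first pass, when access has already been made.
- *This is the bleeding type on which the arms differ most.* Nothing in the protocol ranks bleeding types in that way. Its stated concern is mainly intracranial hemorrhage.
- *A particular excess is being missed.* No rate is given from which one could be estimated.

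The reply does not close the remaining gap. XIII defers to the protocol, and section VIII sets procedures only for SAEs and SUSARs. VI.8.2 reaches only patients who withdraw. Intraoperative complications end with the operation, although VI.10.4 is headed 0-24 h. Low power applies equally to the uncommon bleeds already listed, so it is no reason to leave this one out.

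**Conclusion.** The point holds in a limited form. Puncture-site and other extracranial bleeds that arise after the procedure and meet no SAE criterion have no systematic collection route, and the comparison of adverse reactions in XI.3 would be incomplete for them. This is a gap in safety collection. No stated figure is wrong, and no two passages contradict each other.

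The number of events affected cannot be derived from the documents. With 100 per arm, each 1% of patients with such a bleed is one event per arm. The conclusion rests on reading the 24-72 h list as complete and on the unseen case report form following it. If the form already has an item for other bleeding, only the protocol text needs aligning. The primary outcome and the sample size are unaffected.

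**What to change.** In VI.10.5.1, add to the list: *puncture-site or retroperitoneal bleeding/haematoma, and any other bleeding (site, date, intervention needed)*. Ask it of every patient in both arms, covering the time from the start of treatment to the 24-72 h visit. Add a matching row to the flow chart in VII. Report any extracranial bleeding by arm, as counts and percentages with a confidence interval for the difference, as description rather than as a test.

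The cost is one or two case report form items at a visit that already takes place, one table and slightly more data entry. Patients already enrolled can be completed from hospital notes, but ascertainment will be less uniform than prospective questioning, so the report should say which patients were completed that way. Power stays low, as shown in the working. The change alters no treatment rule.

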### **10.5.2 Discharge assessment form (up to 90-day at the latest)**

On the day of discharge or death, confirm and record the contact details of the patient or the caregiver for follow-up evaluation in the future.

The following shall be recorded:

- Discharge time
- GCS, NIHSS, and mRS scores at discharge

### **10.5.3 90 days ( $\pm 7$ )**

- mRS score

These assessments should be conducted by an investigator who was not involved in the clinical management of patients and is blinded to the randomized treatment allocation.

At 90-day  $\pm 7$  days, all surviving patients will be consulted and evaluated by telephone or face-to-face.

### **10.5.4 Death**

If the patient dies before the planned follow-up time, details of the cause of death of the patient, including the date and time of death, shall be recorded. Copies of autopsy reports, admission records, or death certificates should be kept together with the participant contact form for monitoring by the leading center.

## ***10.6 Discontinuation of assigned treatment and protocol violation***

The leading center will provide a form to record the date and details of deviations from the protocol or missing assessments.

### ***10.7 Informed consent***

The process of informed consent should be recorded in the patient's medical record and case report form. The type of informed consent obtained should be recorded in the database.

### ***10.8 Serious adverse events***

All SAEs shall be recorded in the SAE form and reported to the leading center within the specified time by fax or e-mail. Additional information on events and outcomes may be requested.

## **VII. Study flow chart**

| Evaluation                       | Baseline
(screening
and
enrollment) | Treatment
period
(0-24
hours) | 24-72
hours after
randomizat
ion | At discharge
(up to 90
days at the
latest) | Day 90 $\pm$ 7
(Final
visit) |
|----------------------------------|----------------------------------------------|----------------------------------------|-------------------------------------------|-----------------------------------------------------|------------------------------------|
| Informed consent                 | X                                            |                                        |                                           |                                                     |                                    |
| Demographic characteristics      | X                                            |                                        |                                           |                                                     |                                    |
| Symptoms of this stroke          | X                                            |                                        |                                           |                                                     |                                    |
| Medical history                  | X                                            |                                        |                                           |                                                     |                                    |
| Concomitant medication           | X                                            | X                                      | X                                         | X                                                   |                                    |
| Critical time        | X                                            | X                                      |                                           |                                                     |                                    |
| Vital signs                      | X                                            | X                                      |                                           |                                                     |                                    |
| Laboratory examination           | X                                            |                                        | X                                         |                                                     |                                    |
| Electrocardiogram                | X                                            |                                        |                                           |                                                     |                                    |
| Inclusion and exclusion criteria | X                                            |                                        |                                           |                                                     |                                    |
| Randomization                    | X                                            |                                        |                                           |                                                     |                                    |
| Imaging examination              | X                                            |                                        | X                                         |                                                     |                                    |
| Tirofiban treatment information  |                                              | X                                      |                                           |                                                     |                                    |
| Thrombectomy information         |                                              | X                                      |                                           |                                                     |                                    |
| mRS                              | X                                            |                                        |                                           | X                                                   | X                                  |
| NIHSS                            | X                                            |                                        | X                                         | X                                                   |                                    |

|      |   |   |   |   |   |
|------|---|---|---|---|---|
| GCS  | X |   | X | X |   |
| SAEs |   | X | X | X | X |

1.critical time: onset time (or last seen well time) at randomization assessment, time of admission, time of CTP; The start time of tirofiban intravenous bolus, the start time of intravenous infusion, the end time of intravenous infusion, the femoral artery puncture time, the first DSA angiography time, and the final recanalization time of endovascular treatment.

